## Sample Size Considerations

Enrollment target for arms 1 and 3 will be 60 evaluable subjects (those completing study endpoints). Arm 2 will be used as a comparator for the 4 mg/kg study cohort tested in the study conducted in 2006. Subjects will be enrolled in the 3 groups at a ratio of 2:1:2. The dropout rate is expected to be approximately 25%. Any dropouts (e.g. withdrawals, lost-to-follow-ups etc.) will be replaced in the same arm. Therefore 190 persons may be enrolled to achieve 150 evaluable subjects. In case the enrollment target of 150 evaluable subjects cannot be met within the approved study duration an application for extension of the study duration will be filed.

Arm 2 serves as a control and will serve as a bridge to the study performed in 2006/2007. The sample size in this arm is lower as results from 60 evaluable patients are available from the earlier study conducted at the same site.

The sample size for detecting a significant difference between the 2 study arms by uncorrected Chi2-test is calculated based on an expected cure rate (i.e. early and late treatment failures) of 80% in arm 1 and 95 % in arm 3:

α 0.1

1 – β 0.8

p0 0.8

p1 0.95

Calculated sample size per arm 59

With 60 patients in arm 1 and 60 patients in arm 3 there will be a >80% chance of detecting a significant difference by uncorrected Chi2-test at a two sided 0.1 significance level. This assumes that the response rate in arm 1 is 0.8 and the response rate in arm 3 is 0.95.

Figure 1: Case sample size relative to power for α = 0.1 (Dupont and Plummer 1997)

[figure not shown]

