## Randomization Procedures

Subjects will be assigned unique identification codes (ARC08 followed by a 3 digit number) in order of inclusion and randomly assigned to either one of the artesunate groups. The ratio of enrollment into the three groups is 2:1:2. Randomization will not be stratified and will be done using random number tables in blocks of 10. A randomization list will be created prior to beginning the trial. Sealed individual envelopes that will be opened only on enrollment of each subject will be used. The study personnel enrolling the subject will therefore not know which group the patient will be assigned to until opening the envelope.

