# Statistical Considerations

## Study Outcome Measures and Analysis

The primary outcome for the clinical part of the study will be cure rates in arms 1 and 3. Cure rates will be analyzed separately for Day 28 and 42.

The primary outcome of this study is a nominal variable: the treatment will be characterized as successful or unsuccessful/resistant. Cure rates will be summarized along with 95% confidence intervals (exact based on binomial distribution). The resulting categorical frequency data between arm 1 and 3 will be compared in Chi2-tests.

The secondary endpoints of this study are continuous variables. Overall group differences between secondary endpoints of parasite clearance time (PCT), gametocyte clearance time (GCT), and fever clearance time (FCT) will be compared using the Mann-Whitney U test. In vitro data will be analyzed by nonlinear regression models. The alpha level for tests used to compare differences between treatment groups will be 5%.

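### Replacing dropouts in the same arm lets who dropped out decide the replacement's treatment, in conflict with concealed random assignment for up to 40 of 190 subjects

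*Protocol*

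**What the plan says.** Protocol section 11.2 (Sample Size Considerations) sets the replacement rule: "Any dropouts (e.g. withdrawals, lost-to-follow-ups etc.) will be replaced in the same arm". The same section sets the target, "Enrollment target for arms 1 and 3 will be 60 evaluable subjects (those completing study endpoints" (the bracket is its definition of evaluable), the ratio, "Subjects will be enrolled in the 3 groups at a ratio of 2:1:2", the expected dropout, "The dropout rate is expected to be approximately 25"%, and the total, "Therefore 190 persons may be enrolled to achieve 150 evaluable subjects".

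Section 5.5 (Randomization Procedures) describes a list made before the trial, unstratified, in blocks of 10, with sealed envelopes opened at enrolment. It concludes: "The study personnel enrolling the subject will therefore not know which group the patient will be assigned to until opening the envelope". It says nothing about replacements. Section 11.3 repeats the 190 and says that participants are assigned at random to the three groups. Section 4 states that the trial is open label, and section 5.2 that in-patient care is given at Tasanh Health Center.

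Section 11.1 compares cure rates between arms 1 and 3 by chi-square test and names no analysis population.

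**The concern.** Under a list and sealed envelopes, chance decides the next subject's arm and nobody can foresee it. Under same-arm replacement, the previous departure decides it. Staff who know that a subject in a given arm has left can know which arm the next replacement will enter while they are still deciding whom to approach and whether to enrol. That opens the door to selection at entry, which concealment exists to close. It cannot be repaired at analysis, because no later plan can restore an allocation that was foreseeable when it was made.

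A second question follows from the first. If withdrawals are replaced and the target counts completers, the status of subjects who stop the drug for toxicity matters. They are either evaluable members of their arm or dropouts exchanged for someone else. Section 4 says that arm 3 receives a total dose above any previously studied in humans, so the protocol should not leave this open.

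**Working it through.** **1. The plan's own figures.** The inputs, all from section 11.2, are cure 0.80 in arm 1 and 0.95 in arm 3, two-sided alpha 0.10, power 0.80 and an uncorrected chi-square test.

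- Mean rate = (0.80 + 0.95)/2 = 0.875.
- n per arm = [1.645 × √(2 × 0.875 × 0.125) + 0.842 × √(0.80 × 0.20 + 0.95 × 0.05)]² / 0.15² = (0.769 + 0.383)² / 0.0225 ≈ 59.05, or 60 when rounded up. The stated 59 reproduces.
- Power with 60 per arm = 0.806. The stated figure of more than 80% reproduces.
- Enrolment: 150 × 1.25 = 187.5, close to the stated 190. Dividing by the completing fraction gives 150/0.75 = 200. So 190 corresponds to 1 − 150/190 = 21.1% dropout, not 25%.

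The 60 per arm that carry this power are evaluable subjects by definition.

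**2. Share of subjects who could be replacements.**

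- At the stated enrolment: 190 − 150 = 40, and 40/190 = 21.1%. With equal dropout across arms this is 16 of 76, 8 of 38 and 16 of 76.
- At a true 25% dropout: 200 − 150 = 50, and 50/200 = 25%.

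**3. The allocation statements side by side.** Section 5.5 says the next envelope decides and nobody knows the arm beforehand. Section 11.3 says assignment is random. Section 11.2 says the replacement goes to the arm of the subject who left. The protocol gives no mechanism. The obvious ones are that the next patient takes the vacancy, that envelopes are reserved for each arm, or that each arm is topped up to its target. Each makes the arm known or predictable to anyone who knows which arm lost a subject.

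**4. The status of a subject stopped for toxicity.**

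- Section 9.4, individual halting rules: the subject is withdrawn from the randomised dosing arm and gets no more artesunate. Leaving the study is not mentioned.
- Rescue Treatment (section 6): subjects who do not complete dosing for safety or tolerability are followed to Day 42.
- Section 7.4: a subject may be discontinued from the study, for example for intolerance or an SAE needing referral, and the text points to the halting rules in 9.4.
- Section 11.2: withdrawals are dropouts and are replaced.
- Section 8.1.1: no failure category covers stopping for toxicity, so a subject cleared by rescue drugs could be classed as a cure.

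One halted subject can therefore be read as evaluable and cured, as evaluable with an undefined outcome, or as a replaced dropout.

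**5. How much the counting rule can matter (illustration only).** Assume completers give 48/60 in arm 1 and 57/60 in arm 3. The uncorrected chi-square is 6.17, p = 0.013.

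- Add eight withdrawals counted as failures to arm 3 only: 48/60 against 57/68 (83.8%), chi-square 0.32, p = 0.57.
- Add the eight to arm 1 only: 48/68 (70.6%) against 57/60, chi-square 12.9, p < 0.001.

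The eight are invented. The two cases show that the rule for counting withdrawals can change the result in either direction. They do not measure the effect of replacement itself.

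**The case against.** The best defence has four parts.

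- **No mechanism is stated.** Section 11.2 gives no timing, staff role or procedure for replacement, section 11.3 still says assignment is random, and 190 is a ceiling. This stands as a limit on certainty: 40 is a planning maximum, and actual foreknowledge is an inference. It does not remove the conflict, because the only replacement rule in the protocol is specific to the arm.
- **Outcome reading is protected.** Section 6.2.3 blinds the microscopists to treatment. That helps with assessment of parasitaemia, but not with who enters which arm.
- **Losses may be mostly unrelated to dose.** In the previous trial at this site, 4 mg/kg showed no artesunate toxicity and no SAEs. Haematology was available for 71 of 73 artesunate subjects at Day 7, while 60 were evaluable, so loss seems to have come mainly after dosing. This is fair. But a loss to follow-up is also replaced in the same arm, so the allocation problem is the same.
- **The analysis set may be fixed elsewhere.** Section 11.1 names none, and a statistical analysis plan may exist. This stands: counting only completers is certain for the target and the power, not for the test.

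Three stronger readings are tempting, and the protocol does not support them.

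- A reader might infer that toxicity withdrawals necessarily leave the comparison. The rescue section follows them to Day 42, and nothing removes them from the adverse-event outcome.
- A reader might infer that the bias favours arm 3. Poor response is an endpoint under sections 4 and 8.1.1 and not a cause of dropout. If poor responders did leave arm 1 early, that would raise its completer cure rate and work against arm 3.
- A reader might take worst-case and best-case cure rates over the missing subjects as the harm done by replacement. Those limits come from the missing data and would be as wide without any replacement rule.

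**Conclusion.** The point holds for allocation. Same-arm replacement contradicts sections 5.5 and 11.3. In an open-label trial with one in-patient site, it lets a replacement's arm be known before enrolment. By the protocol's own figures it could affect up to 40 of 190 subjects (21%), or 50 of 200 (25%) if dropout is truly 25%. The per-arm split of 16, 8 and 16 assumes equal dropout.

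It also holds that sections 6 (Rescue Treatment), 7.4, 9.4 and 11.2 leave open whether a subject stopped for toxicity is evaluable or is replaced, while the target and power rest on completers. The size and direction of any resulting bias cannot be stated from the documents. The rule should be changed before enrolment, since a later analysis plan can define the population but cannot restore concealment.

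**What to change.** - In section 11.2, delete the rule that dropouts are replaced in the same arm.
- Prepare the 2:1:2 list in blocks of 10 in advance for the full planned enrolment, and give every new subject the next envelope until the total is reached. Nineteen blocks give 190 (76/38/76). Twenty give 200 (80/40/80), which matches 25% dropout as 150/0.75 but requires the 190 in sections 11.2 and 11.3 to be changed.
- Compare arms 1 and 3 in all randomised, treated subjects as assigned, with a rule stated beforehand for counting withdrawals and toxicity stops. Keep the completer chi-square as supportive. Censoring withdrawals in a time-to-event analysis would not be enough on its own, because it assumes that leaving is unrelated to outcome.
- Reconcile sections 5.5, 7.4, 9.4, 11.2, 11.3 and the rescue section, so that it is clear who has left the study, who has only left the dosing arm, and who is evaluable.

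The cost is an amendment, which section 14.2 sends to all review boards, plus some envelopes. Evaluable numbers will no longer be exactly 60/30/60. With 76 randomised and independent dropout of 21.1%, the standard deviation of the evaluable count is √(76 × 0.789 × 0.211) ≈ 3.6 in arms 1 and 3. In arm 2 it is √(38 × 0.789 × 0.211) ≈ 2.5.

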## Participant Enrollment and Follow-Up

190 persons may be enrolled to achieve 150 evaluable subjects. Study participants will be randomly assigned to one of three treatment groups and followed for 42 days.

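### Enrolling 190 does not give 150 evaluable subjects at the stated 25% dropout: that needs about 200, and 190 allows for only 21%

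*Protocol*

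**What the plan says.** Section 11.2 (Sample Size Considerations) sets the target in evaluable subjects: "Enrollment target for arms 1 and 3 will be 60 evaluable subjects (those completing study endpoints"), with 150 across the three arms. Allocation is fixed: "Subjects will be enrolled in the 3 groups at a ratio of 2:1:2".

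The allowance for losses follows in three steps. First the rate: "The dropout rate is expected to be approximately 25" per cent. Then the replacement rule: "Any dropouts (e.g. withdrawals, lost-to-follow-ups etc.) will be replaced in the same arm". Then the conclusion: "Therefore 190 persons may be enrolled to achieve 150 evaluable subjects". Section 11.3 (Participant Enrollment and Follow-Up) repeats it: "190 persons may be enrolled to achieve 150 evaluable subjects".

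For the case where the target is missed, section 11.2 offers more time: "In case the enrollment target of 150 evaluable subjects cannot be met within the approved study duration an application for extension of the study duration" is to be filed. It gives no enrolment number above 190.

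The power claim rests on 60 subjects in arm 1 and 60 in arm 3, with cure rates of 80% and 95%: "there will be a >80% chance of detecting a significant difference by uncorrected Chi2-test at a two sided 0.1 significance level".

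**The concern.** A dropout rate is normally a share of those who enter the trial, and section 11.2 gives no other base. On that base 190 is too few for 150. The figure looks as if the 25% was applied to the evaluable target, which is a common slip and always gives too small a number.

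Two things are at stake. The first is whether the enrolment number that the review boards see is the number the plan needs. The second is power. The calculated size is 59 per arm and the target 60, so there is almost no slack, and a small shortfall in arms 1 and 3 takes the power below the stated 80%.

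**Working it through.** **Inputs, all from section 11.2:** 150 evaluable in total; 60 evaluable in each of arms 1 and 3; dropout d = 0.25; ratio 2:1:2; cure rates 0.80 and 0.95; two-sided alpha 0.10; uncorrected chi-square test; power 0.80.

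**1. The plan's per-arm size reproduces.** With mean cure rate 0.875:

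- √(2 × 0.875 × 0.125) = 0.4677
- √(0.80 × 0.20 + 0.95 × 0.05) = 0.4555
- n = [(1.645 × 0.4677 + 0.842 × 0.4555)/0.15]² = 59.05

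The protocol reports 59; rounding up gives 60. The power formula is Φ{(0.15√n − 1.645 × 0.4677)/0.4555}. At n = 60 this is Φ(0.862) = 80.6%, which agrees with the stated power above 80%.

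**2. The plan's enrolment figure does not reproduce on the usual base.**

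- Dropout as a share of those enrolled: 150/(1 − 0.25) = 200.
- Dropout added to the evaluable target: 150 × 1.25 = 187.5, which rounds up to 190.

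The protocol does not show its derivation, but the second line comes close to the stated number and the first does not.

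**3. What the second line omits.** Replacing 25% of 150 takes 37.5 further subjects, giving 187.5. A quarter of those replacements would also drop out (37.5 × 0.25 = 9.4), giving 196.9 after a second round. The series continues to 150/0.75 = 200.

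**4. What 190 delivers.**

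| Dropout among enrolled | Evaluable from 190 | Enrolment needed for 150 |
| --- | --- | --- |
| 20% | 152.0 | 187.5 |
| 21% | 150.1 | 189.9 |
| 22% | 148.2 | 192.3 |
| 25% | 142.5 | 200.0 |

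The break-even rate is 1 − 150/190 = 40/190 = 21.05%. If each of 190 subjects had a 25% chance of dropping out independently, the binomial probability of at least 150 evaluable would be about 12%.

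**5. By arm, if enrolment stopped at 190.** At 2:1:2, 190 is 76/38/76. Multiplying by 0.75 gives 57/28.5/57. For 200 the split is 80/40/80, giving 60/30/60.

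**6. Power in arms 1 and 3 at two-sided alpha 0.10.**

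- 60 per arm: 80.6%
- 59 per arm: Φ(0.840) = 80.0%
- 57 per arm: Φ(0.797) = 78.7%

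The difference between 60 and 57 per arm is 1.9 percentage points.

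**The case against.** The strongest reply is that the target is set in evaluable subjects, dropouts are replaced, and more time will be sought if 150 cannot be reached. Read together, this describes recruiting until 150 are evaluable, in which case arms 1 and 3 reach 60 and the power is kept. That stands as an answer on power. It does not rescue the number: the sentence giving 190 is drawn as a conclusion from the dropout rate and the replacement rule, so replacements are already counted in it. The extension clause concerns duration and states no larger enrolment.

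A second reply is that the wording is loose: the rate is approximate, and 190 is a number that may be enrolled. A true rate near 21% would make 190 right. But the protocol says 25% and derives 190 from it, and section 7.2 says that the sample size calculations allow for a projected loss rate.

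A third reply is that the protocol's own earlier data suggest smaller losses. In ARC1 at the same site, the laboratory safety tables show 73 artesunate patients at Day 0, and the Day 28 cure rate rests on 60, so 13/73 = 17.8% were not evaluable. At that rate 190 would yield 190 × 60/73 = 156. This shows that a shortfall is not certain. It is weak support for the figure, however, because the ARC1 cure rate was at Day 28 and patients stayed on site for 21 days, whereas follow-up here runs to Day 42.

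A reader might also infer that 190 is an approved ceiling, so that the trial must stop short of 60 per arm. The protocol does not say so: it nowhere calls 190 a cap, and in section 11.2 only the study duration is described as approved.

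**Conclusion.** The point holds as an arithmetic inconsistency in sections 11.2 and 11.3. With dropout taken as 25% of those enrolled, the stated enrolment is 10 below the 200 needed, or 5%. Equivalently, 190 allows for 21% dropout and not 25%.

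The effect on the trial is conditional and small. Only if enrolment stops at 190 and dropout is 25% does the expected yield fall to about 142 evaluable, three short in each of arms 1 and 3, with power at 78.7% instead of above 80%. This rests on the protocol's assumed cure rates and a normal approximation. If replacement continues to 150 evaluable, there is no loss of power. The documents do not support the stronger reading that the trial will be underpowered because of this figure.

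Nor should this point be charged with the lower power at a 5% test level. With 57 per arm that power is 68.2%, but with 60 per arm it is already only 70.5%. Almost all of that gap comes from a separate conflict, between the 5% level in section 11.1 and the alpha of 0.10 in section 11.2. The dropout arithmetic again accounts for only about 2 points.

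**What to change.** Make the dropout rate, the enrolment number and the evaluable target agree in both sections, in one of two ways:

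- **Change the number.** State that about 200 persons (80/40/80) are expected to be enrolled to reach 150 evaluable at 25% dropout, with replacement in the same arm until the target is met.
- **Change the assumption.** Keep 190, state that it allows for about 21% dropout, and give the power of 78.7% at two-sided alpha 0.10 that would result if dropout is 25% and enrolment stops at 190.

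The second option costs a slightly less favourable stated figure. The first needs review board approval of up to 10 more subjects, four of them in arm 3. Section 14.2 requires all amendments to be approved by all the review boards, so either change is an amendment, although the edit itself is confined to a few lines in two sections.

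### The stated power of more than 80% is calculated at a two-sided 10% level, but the analysis section tests at 5%, where power is about 70%

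*Protocol*

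**What the plan says.** Section 11.1 (Study Outcome Measures and Analysis) names cure in arms 1 and 3 as the primary clinical outcome and gives the test: "The resulting categorical frequency data between arm 1 and 3 will be compared in Chi2-tests". The section gives one significance level, at its end: "The alpha level for tests used to compare differences between treatment groups will be 5" per cent. It does not say whether the test is one- or two-sided. Confidence intervals for the cure rates are 95%.

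Section 11.2 (Sample Size Considerations) sizes the same two arms for the same endpoint and test. It lists an alpha of 0.1 and a power of 0.8, and reports "Calculated sample size per arm 59". It concludes that with 60 in each arm "there will be a >80% chance of detecting a significant difference by uncorrected Chi2-test at a two sided 0.1 significance level". On the cure rates it says: "This assumes that the response rate in arm 1 is 0.8 and the response rate in arm 3 is 0.95". Figure 1 is also captioned for alpha = 0.1. The target of 60 counts evaluable patients, and on losses the section says: "Any dropouts (e.g. withdrawals, lost-to-follow-ups etc.) will be replaced in the same arm".

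**The concern.** The power statement and the analysis rule describe two different tests of one comparison. If the primary test is run at 5%, as Section 11.1 reads, the figure of more than 80% does not belong to it.

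Two things are at stake:

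- **Reading a null result.** This comparison addresses the principal aim, whether higher doses overcome reduced artemisinin sensitivity. A non-significant result judged against a power of more than 80% would look like stronger evidence against a dose effect than the design can supply.
- **The rejection rule itself.** A p-value between 0.05 and 0.10 is significant under Section 11.2 and not under Section 11.1. If this stays open, the level could be chosen after the data are seen.

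**Working it through.** **Inputs.** All come from Section 11.2 except the 5% level, which is from Section 11.1.

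- Cure 0.80 in arm 1 and 0.95 in arm 3: difference 0.15, mean 0.875.
- 60 evaluable per arm. Dropouts are replaced in the same arm, so 60 is the right number for power.
- Chi-square test without continuity correction, two-sided, equal arms.
- Normal quantiles: 1.6449 (two-sided 10%), 1.9600 (two-sided 5%), 0.8416 (80% power).

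**Formulas** (normal approximation, pooled variance under the null):

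- n per arm = [z(1−α/2)·√(2·p̄·q̄) + z(0.8)·√(p₀q₀ + p₁q₁)]² / (p₁ − p₀)²
- power = Φ{[√n·(p₁ − p₀) − z(1−α/2)·√(2·p̄·q̄)] / √(p₀q₀ + p₁q₁)}

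with √(2 × 0.875 × 0.125) = 0.4677 and √(0.16 + 0.0475) = 0.4555.

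**Step 1: reproduce the protocol's figure (two-sided 10%).**

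- n = (1.6449 × 0.4677 + 0.8416 × 0.4555)² / 0.0225 = (0.7693 + 0.3834)² / 0.0225 = 59.05. The protocol states 59.
- Power at 60 per arm = Φ[(1.1619 − 0.7693) / 0.4555] = Φ(0.862) = 80.6%. The protocol states more than 80%.

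Other bases do not give 59: a one-sided 10% test gives 43, and a continuity-corrected two-sided 10% test gives 72. The calculation therefore did use an uncorrected two-sided 10% test, as the text says.

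**Step 2: the same design at two-sided 5%.**

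- Power at 60 per arm = Φ[(1.1619 − 0.9167) / 0.4555] = Φ(0.538) = 70.5%.
- n for 80% power = (0.9167 + 0.3834)² / 0.0225 = 75.1, so 76 per arm.

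**Step 3: exact check.** Summing the binomial probabilities of every pair of outcomes for which the uncorrected chi-square exceeds its critical value gives:

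| 60 per arm, 80% vs 95% | Two-sided 10% | Two-sided 5% |
|---|---|---|
| Power, planning formula | 80.6% | 70.5% |
| Power, exact enumeration | 83.0% | 73.0% |
| Chance of missing the effect, formula | 19.4% | 29.5% |
| Chance of missing the effect, exact | 17.0% | 27.0% |

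**Step 4: what 60 per arm can detect at two-sided 5%.** With 95% cure in arm 3, power reaches 80% when cure in arm 1 is 77.6% by the formula, or about 78.3% by exact enumeration, in place of the planned 80%.

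**Step 5: an outcome on which the sections disagree.** Suppose 57/60 are cured in arm 3 and 51/60 in arm 1. The difference is 0.10 and the pooled rate 0.90, so chi-square = 0.01 / (0.90 × 0.10 × 2/60) = 3.33 and p = 0.068. That is significant at the level in Section 11.2 and not at the level in Section 11.1.

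**The case against.** The strongest reply is that the protocol does not say outright that the primary test uses 5%. The value 0.1 appears three times in Section 11.2 (input list, power sentence, figure caption), so it looks deliberate, and it is the only level tied by name to the comparison of arms 1 and 3. The 5% sentence closes the paragraph on secondary endpoints and in vitro data. On that reading the power statement is correct, and the primary test is simply meant to run at 10%.

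Part of this stands: 0.1 is not a misprint, and the calculation contains no numerical error. But the 5% sentence is worded for tests of differences between treatment groups in general, the primary chi-square is such a test, and the analysis section gives no other level. If 10% was intended for the primary test, Section 11.1 needs correcting instead.

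A one-sided 5% test would restore 80.6%, but the text does not support it: Section 11.2 says two-sided, the chi-square test is non-directional, and the intervals are 95%.

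It is also fair that exact power is 73.0%, that the detectable arm 1 rate moves only about two percentage points, and that exact 95% intervals will show the imprecision. These points limit the harm. They do not make the stated power that of a 5% test.

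**Conclusion.** The concern holds. The protocol gives two significance levels for its primary comparison, and the power claim is true only at the one that the analysis section does not use. At two-sided 5% with 60 evaluable per arm and cure rates of 80% and 95%, power is 70.5% on the formula that reproduces the protocol's own sample size and 73.0% by exact enumeration. That is roughly ten percentage points below the matching figures at 10%. The planned 60 per arm is 16 short of the 76 that the formula requires for 80% power at 5%.

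This rests on reading the 5% sentence as covering the primary test and on a two-sided test. If 10% is what the sponsor means, the power figure stands and the analysis section is the text in error. The protocol needs correction in either case, before outcome data are seen.

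**What to change.** State one significance level for the comparison of arms 1 and 3, in the same terms in Sections 11.1 and 11.2, and say that it is two-sided.

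The recommended route keeps 5% and replaces the power statement with, for example: *With 60 evaluable patients per arm and a two-sided alpha of 0.05, the uncorrected chi-square test has about 70% power for cure rates of 80% versus 95% (normal approximation; 73% by exact enumeration); 80% power is reached for 77.6% versus 95% (normal approximation; about 78.3% by exact enumeration).* The listed alpha, the calculated sample size and Figure 1 should be redone at 0.05 to match.

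The cost is one paragraph and one figure, with no extra patients. The price is a less favourable power figure.

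Two other routes would also remove the conflict:

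- Raise the target to 76 evaluable patients in each of arms 1 and 3, which adds 2 × 16 = 32 evaluable patients in those arms.
- Declare in Section 11.1 that the primary comparison is tested at a two-sided 10% level. This leaves the power statement true but accepts a 10% false-positive rate for the primary test, which should then be justified.
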